## Methods

### Study Design

This is a retrospective cohort study using data from the nationally representative Primary Care Sentinel Cohort (PCSC) of the Oxford-Royal College of General Practitioners (RCGP) Research and Surveillance Centre (RSC) [14]. The RSC is one of Europe’s oldest sentinel systems, and hepatitis is one of its 32 monitored conditions [15]. The database has previously been used for liver disease and hepatitis research [3,16].

We will use electronic health record data for the period between January 1, 2012, and December 31, 2022. Data will be extracted retrospectively at the time of the beginning of the study.

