#### Covariates

Sociodemographic characteristics will be reported closest to the earliest date of CLD diagnosis as baseline, within a 10-year range for time-sensitive variables. These include age, gender, ethnicity (categorized into White, Black, Asian, multiracial, and other), rurality (measure of population density), region, socioeconomic status (measured using the index of multiple deprivation), obesity, alcohol consumption, and smoking. A history of comorbid conditions and complications will be extracted from 10 years of computerized medical records, including osteoporosis, bile duct and colon cancers, renal disease (including calculi), ascites, liver failure and transplant, and cardiometabolic disease. The CMMS will be used to report on comorbidity profiles [26,27].

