#### Reporting Predictors of 1 and 2 Doses of Hep A Vaccination in People With CLD

##### Overview

A multistate model will be used on a retrospective cohort of individuals identified in the ORCHID diagnosed with CLD. People enter the study on the first diagnosis of CLD, and we will model the transition probabilities between the identified states: diagnosed with CLD, first dose of Hep A vaccination, second dose of Hep A vaccination, and death (Figure 2).

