**Figure 2 figure2:**

State transition diagram for competing risks multistate model for a retrospective cohort of adults with chronic liver disease (CLD) in England between January 1, 2012, and December 31, 2022, evaluating hepatitis A (Hep A) vaccination with 1 and 2 doses as outcomes and death as a competing risk represented as an absorbing state.

A multistate survival model will be fitted to estimate the transition probabilities between the 4 identified study states (Figure 2). The states are (1) diagnosis of CLD, (2) first dose of Hep A vaccination, (3) death, and (4) second dose of Hep A vaccination. The outcome of interest is the Hep A vaccination. Therefore, the state of a second dose of Hep A vaccination is a censored state, with no further transitions to death; the moment a patient receives 2 doses of Hep A vaccination, the follow-up ends. Death is an absorbing state, with no further transitions allowed. Death is included as a competing risk for vaccination, not as an outcome. This means that when calculating the transition probabilities to vaccination, we adjust for when a person is not vaccinated because of death before vaccination rather than for any other predictors of nonvaccination.

Patients lost to follow-up will be right censored and evaluated accordingly as per the likelihood function of the “msm” R package [30].

Multistate probabilities are based on the same assumptions as a Markov process:

The health states considered in the model are thorough and mutually exclusive.The probability to move from one health state to following states only depends on (is conditioned on) the health state of the individual at transition time (memoryless process).Transition probabilities are steady over time.

The state transition probabilities will be estimated conditional on the study risk factors. Study risk factors include (1) etiology of CLD (eg, ALD, CH-B, CH-C, and NAFLD); (2) sociodemographic characteristics (eg, age, sex, ethnicity, deprivation, obesity, smoking, and alcohol consumption); (3) CLD complications (eg, bile duct and colon cancers, renal disease, ascites, liver failure and transplant, and cardiometabolic disease); and (4) comorbidities (eg, CMMS, bile duct and colon cancers, at least 3 doses of COVID-19 vaccine, and flu vaccination).

The multistate model will be estimated using the “msm” (version 1.6.9) package in R [31].

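### The multistate model conditions on having at least three COVID-19 vaccine doses, a value most of a 2012-2022 cohort cannot have at entry, and the plan gives no time-dependent handling

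*Protocol article*

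**What the plan says.** Under the predictors heading (Overview), "People enter the study on the first diagnosis of CLD". Study Design sets the period: "We will use electronic health record data for the period between January 1, 2012, and December 31, 2022". The text under Figure 2 states that "The state transition probabilities will be estimated conditional on the study risk factors", and its list of comorbidities ends with "at least 3 doses of COVID-19 vaccine, and flu vaccination". The Objectives also name these vaccinations, as exposures by which coverage is to be reported.

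The same Figure 2 text makes the model memoryless, with the assumption that "Transition probabilities are steady over time". On mortality it says "Death is included as a competing risk for vaccination, not as an outcome".

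Covariates gives the only timing rules. For sociodemographic variables: "Sociodemographic characteristics will be reported closest to the earliest date of CLD diagnosis as baseline, within a 10-year range for time-sensitive variables". For clinical history: "A history of comorbid conditions and complications will be extracted from 10 years of computerized medical records". Neither rule mentions COVID-19 or flu vaccination, and neither says whether the ten years run before or after diagnosis. No section mentions a time-dependent covariate.

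**The concern.** A covariate in a time-to-event model must be known at the start of the person-time to which it is applied. Someone diagnosed in 2014 could have three COVID-19 doses only by living, and staying registered, until years later. If that later status is attached to the whole of follow-up from 2014, the vaccinated group's earlier person-time cannot contain a death. This is immortal time.

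The consequence is specific to this design. The declared output is a set of transition probabilities with death competing against vaccination. A false difference in death intensity becomes a false difference in the probability of receiving hepatitis A vaccine, even when the two vaccinations are unrelated. The study could report COVID-19 vaccination as a predictor of hepatitis A vaccination on that basis alone.

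The undated flu vaccination, and the undirected ten-year rule for the other covariates, leave room for a milder form of the same problem.

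**Working it through.** The plan gives no figure of its own on this point. The inputs from the protocol are entry at first CLD diagnosis, the window of 1 January 2012 to 31 December 2022 (11 years), the COVID-19 covariate, and death as a competing state. All rates, uptake and vaccine dates below are assumptions.

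**Share of the cohort entering too early to have the value.** With uniform entry over 11 years:
- before 2020: 8/11 = 73%
- before late 2021 (taken as 2021.75): 9.75/11 = 89%

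**Null simulation of transition probabilities.** Entry is uniform. Hepatitis A dose 1 occurs at 5% a year and death at 5% a year for everyone. Of those alive in late 2021, 70% receive three COVID-19 doses, with no effect on anything. Constant intensities are then fitted by ever/never COVID-19 status.

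| Group | Dose 1 intensity (λ) | Death intensity (μ) |
|---|---|---|
| Without three doses | 0.050 | 0.111 |
| With three doses | 0.050 | 0.011 |

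The 10-year probability of dose 1 is λ/(λ+μ) × (1 − e^(−10(λ+μ))):
- without: 0.05/0.161 × (1 − e^(−1.61)) = 0.311 × 0.800 = 24.8%
- with: 0.05/0.061 × (1 − e^(−0.61)) = 0.820 × 0.457 = 37.4%
- truth for both groups: 0.05/0.10 × (1 − e^(−1)) = 0.5 × 0.632 = 31.6%

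In this simulation about 58% of first hepatitis A doses fall before 2020, and 81-82% before late 2021.

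**Range of the false gap.** At 70% uptake, death at 2% a year gives about 31.5% versus 38.6%, and death at 10% a year gives 19.0% versus 35.4%. Over death rates of 2-10% a year and uptake of 50-90%, the gap runs from about 5 points (2%, 50%) to about 21 points (10%, 90%).

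**Rate ratios, ever/never against time-dependent coding.** A second null simulation used dose 1 at 6% a year, death at 2-10% a year, uptake of 50-90%, loss to follow-up of 0-5% a year, and third doses from 2021.25 or 2021.75.

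| Transition | Ever/never coding | Time-dependent coding |
|---|---|---|
| CLD to death | 0.04-0.11 | 0.99-1.02 (0.94 with varying frailty) |
| CLD to dose 1, mortality equal before and after dose 1 | 0.99-1.01 | 0.99-1.01 |
| CLD to dose 1, mortality halved after dose 1 | 1.13-1.31 | 0.99-1.00 |

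The bias is therefore always present in the death transition, and conditional in the dose 1 transition.

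**Look-back, if the Study Design period also limits covariate history.** Available look-back is the smaller of time since 1 January 2012 and 10 years. Its mean under uniform entry is (10²/2 + 10 × 1)/11 = 60/11 = 5.45 years. The share with the full 10 years is 1/11 = 9%.

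**The case against.** The strongest reply is that the protocol never calls these vaccinations fixed covariates. The word baseline in Covariates is attached to sociodemographic characteristics, and a condensed article may leave covariate coding to the analysis plan. This stands in part: fixed coding is an inference. But the covariate and its threshold are named, the cohort's entry rule makes a baseline value impossible for most people, and nothing points to dated updating. The text as written leads to an ever/never flag.

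A second reply is that the hepatitis A intensity itself is unbiased in the simplest null. That is correct, and a reader should not infer that every hazard ratio for vaccination is wrong. It does not clear the plan, because transition probabilities are the stated output and they are distorted throughout the range examined.

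Three stronger readings are tempting but not supported:
- **That the plan takes covariate values from after diagnosis.** The Covariates wording permits this but does not prescribe it, and a history reads naturally as looking back.
- **That ten years of look-back is unavailable.** This follows only if the Study Design dates also truncate covariate records, which the protocol does not say.
- **That adjusting for flu vaccination is an error because it absorbs part of the disparity.** Flu vaccination can precede diagnosis, the stated aim is independent predictors, and coverage by ethnicity and deprivation is also to be reported descriptively. Whether to adjust for it is a modelling choice.

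**Conclusion.** The point holds for the COVID-19 covariate and should be corrected before analysis. Coded ever/never, it conditions on survival and registration to the end of the period. Under a true null this gives a death rate ratio of about 0.04-0.11 and a gap of about 5 to 21 percentage points in the 10-year probability of dose 1. The dose 1 intensity is affected (ratio about 1.13-1.31) only where mortality differs before and after dose 1, as when it is halved.

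These sizes rest on assumed rates, uptake and vaccine dates, on uniform entry, and on the inferred ever/never coding. The direction of the false death effect does not depend on the particular values tried. For flu vaccination, baseline values and clinical history, the finding is an ambiguity to close. No effect size was derived for them.

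**What to change.** 1. Remove COVID-19 doses from the main multistate model and report them descriptively. Alternatively, enter them as a time-dependent covariate dated at receipt, limited to person-time when third doses were possible.
2. Take flu vaccination from a fixed window before diagnosis, or enter it as time-dependent.
3. State in Covariates that baseline values and history are dated on or before CLD diagnosis, with later complications entered as time-dependent.
4. Reconcile Study Design with Covariates so that the ten-year history extends before January 2012.

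The cost is revised wording, a wider date range for covariate extraction, and somewhat more missing baseline values once later records are excluded. The study uses existing records, so no new data collection is needed.

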##### Missing Data

Descriptive analyses will be conducted on the overall study population and applicable subgroups. Data that are not documented in our database will be reported as missing.

Missing data will be presented as a separate category in univariate statistics and compared to the reference category through univariate odds ratios. Missing data categories will be imputed to the reference category if no significant differences are found in the reference category. Missing data categories will be otherwise included in the analysis as an independent category if evidence suggests they are not missing at random; for example, significant differences to the reference category exist.

##### Sensitivity Analysis

We will estimate 2 multistate models by varying the definition of Hep A dose 2. In the first model, the second dose must be administered within 1 year of the first dose; in the second model, dose 2 may occur within 3 years of the first administered dose. A 3-year time window between vaccinations is likely to exclude those who have been recently vaccinated. Hence the need for such a sensitivity analysis. A complete-case analysis to assess any differences due to missing data can be conducted after assessing the missingness of the descriptive data.

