## Introduction

### Overview

Hepatitis A (Hep A) is a viral infection of the liver caused by the hepatitis A virus (HAV). HAV is transmitted through the fecal-oral route, mainly by exposure to contaminated water sources. Hep A outbreaks are uncommon in the United Kingdom, and most people manifest mild to moderate symptoms that tend to resolve, without sequelae, within several months. In high-risk groups, however, such as people with an underlying chronic liver disease (CLD), a superimposed acute infection with HAV can be severe, potentially requiring hospitalization and carrying a higher risk of death. According to the World Health Organization, approximately 100 million Hep A infections occur globally per year, resulting in 15,000 to 30,000 deaths per year [1]. Of these, the number of people with a preexisting CLD diagnosis remains unclear.

CLD largely results from the progressive destruction and regeneration of hepatocytes, leading to fibrosis and cirrhosis, and has a range of etiologies. The most common causes of CLD include alcohol-related liver disease (ALD), chronic hepatitis B (CH-B) infection, chronic hepatitis C (CH-C) infection, and nonalcoholic fatty liver disease (NAFLD), the latter being associated with metabolic syndrome and obesity [2,3]. Deaths in the United Kingdom from CLD have increased annually for the past decade, peaking at 20.6 per 100,000 population in 2020 [4,5], and are expected to surpass the numbers of premature deaths from coronary heart disease [3], CLD-related hospitalizations in the United Kingdom have increased by half, contributing to the £2.1 (US $2.62) billion per year currently spent on treating liver disease [4,6].

The UK’s public health body, the Health Security Agency, and the national guideline body, the National Institute for Health and Care Excellence, recommend preexposure Hep A vaccination to all people with CLD, regardless of the cause [7,8]. The Hep A vaccine series consists of 2 doses, with the second dose at least 6 months after the first.

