### Variables

#### Overview

The study population is those with CLD as an index condition, as defined in the inclusion criteria. The variables will be curated for the identification of CLD-related codes in the computerized medical records of adults registered in the RSC network (Multimedia Appendix 1).

Comparisons will be conducted between population subgroups with different CLD etiologies, sociodemographic characteristics, complications, and comorbidity profiles.

The outcome of the first objective will be the coverage rates of Hep A vaccination among those with CLD.

For the second objective, we will explore significant independent predictors of the following outcomes among those with CLD: (1) one dose of Hep A vaccination and (2) two doses of Hep A vaccination.

Hep A vaccination, as defined by the UK vaccination scheme, includes an initial 0.5 mL for 1 dose, followed by a booster dose of 0.5 mL after 6-12 months. The booster dose may be delayed by up to 3 years if not given after the recommended interval following the primary dose [8]. For this study, we will report boosters administered within 12 months of the first dose for the base case analysis and 3 years from the first dose for a sensitivity analysis. Hep A vaccination in the United Kingdom is available as a monovalent vaccine, as a combined Hep A and hepatitis B vaccine, and as a Hep A and typhoid vaccine [7]. We will consider any Hep A vaccination type as an outcome.

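### Both dose-2 definitions set only an upper time limit, so a second record earlier than the protocol's own minimum interval counts as a completed course

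*Protocol article*

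**What the plan says.** The protocol article describes the vaccination schedule in two places and the study's outcome rule in two places.

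*Schedule.* The Introduction (Overview) states: "The Hep A vaccine series consists of 2 doses, with the second dose at least 6 months after the first". The Variables section (Overview), describing the UK scheme, has a first dose "followed by a booster dose of 0.5 mL after 6-12 months", and adds: "The booster dose may be delayed by up to 3 years if not given after the recommended interval following the primary dose".

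*Outcome rule.* The same Variables section then turns to the study itself: "we will report boosters administered within 12 months of the first dose for the base case analysis", with 3 years from the first dose as the sensitivity analysis. The Sensitivity Analysis section repeats this for the multistate models: "In the first model, the second dose must be administered within 1 year of the first dose", and within 3 years in the second model.

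Three other statements bear on the point. Any vaccine type containing hepatitis A counts towards the outcome (Variables). Follow-up stops when the second dose is reached (the section on predictors of 1 and 2 doses). The check for implausible data is described for covariate values against biological limits (Spurious Data), not for vaccination dates.

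**The concern.** The schedule has a lower and an upper bound; the outcome rule keeps only the upper one. An analyst who codes the rule as stated would accept a second record at one day, one month or five months as dose 2. By the protocol's own description of the series, that is not a completed course.

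Two-dose vaccination is one of the two outcomes of the second objective, and two-dose coverage is to be reported. An early record that is accepted as dose 2 has two effects:

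- It adds a completion that the schedule would not recognise, if the person never receives a qualifying dose.
- It ends follow-up, so any later qualifying dose is not seen and the time to the second dose is recorded as too short.

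The planned sensitivity analysis varies only the upper limit, so comparing the two models gives no warning. The Limitations section accepts that coding errors occur and relies on the large sample to offset them. A large sample reduces random error but does not remove an error built into the outcome definition.

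**Working it through.** The protocol has no figure on early second records, so there is no stated number to reproduce. The check has two parts.

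**1. Classify dose gaps under each rule.** The study rules are 0-12 months (base case) and 0-36 months (sensitivity). The schedule as described in the Introduction and Variables sections gives 6-12 months, or 6-36 months with the permitted delay.

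| Gap between records | Base case as written | 3-year model as written | Schedule 6-12 months | Schedule 6-36 months |
|---|---|---|---|---|
| 1 day; 1, 3 or 5.9 months | counts | counts | no | no |
| 6, 9 or 12 months | counts | counts | yes | yes |
| 13, 24 or 36 months | does not count | counts | no | yes |
| 37 months | does not count | does not count | no | no |

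The first row is the problem. Both models accept these gaps, and neither version of the schedule does.

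**2. Illustrate the effect on two-dose coverage.**

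Inputs from the Introduction (US at-risk adults): any dose, under one-third, taken here as 1/3; both doses, one-fifth, taken as 1/5 and treated as valid completions within both windows.

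Assumed input: *e*, the share of people with one valid dose only who also have a second record below the minimum interval. The documents give no value, so 2%, 5% and 10% are shown.

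People with one valid dose only: 1/3 − 1/5 = 2/15 = 13.3% of the population.

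Reported two-dose coverage = 1/5 + *e* × 2/15:

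- *e* = 2%: 20.0% + 0.02 × 13.3% = 20.3% (+0.3 points)
- *e* = 5%: 20.0% + 0.05 × 13.3% = 20.7% (+0.7 points)
- *e* = 10%: 20.0% + 0.10 × 13.3% = 21.3% (+1.3 points)

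The increase is the same in the base case and the 3-year model, so the difference between the models does not reveal it. With a lower limit in both definitions, coverage returns to 20.0% in each.

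Among first-dose recipients, true completion is (1/5)/(1/3) = 60%. The rule as written gives 60% + *e* × 40%, that is 60.8%, 62.0% and 64.0%.

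People who have both an early record and a later valid dose are already in the 20%. For them the rule leaves coverage unchanged and alters only the recorded time of the second dose.

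**The case against.** The strongest reply is that the minimum is implied. The Variables paragraph opens by defining vaccination according to the UK scheme, with the booster at 6-12 months, and the study rule follows in the same paragraph. On that reading the boosters counted are scheme boosters, and only the outer cut-off varies between models. This reading is possible. However, the sentence that sets the rule for this study and the one in Sensitivity Analysis both omit the minimum, and they are the ones an analyst would program.

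A second reply is that removing repeat entries is routine data processing that a condensed article leaves to a fuller plan. That stands, and the absence of a de-duplication step is no finding here. The point rests on the stated window alone. De-duplication would also leave untouched a genuine second dose given before the minimum interval.

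A reader might infer more than the documents support:

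- *That the base case wrongly codes doses at 13-36 months as incomplete.* The 12-month choice is stated openly, and the 3-year model counts those doses.
- *That recent first-dose recipients will be dropped.* The protocol does say: "A 3-year time window between vaccinations is likely to exclude those who have been recently vaccinated". That wording is loose, but it sets no exclusion rule, and the multistate section right censors patients lost to follow-up. A calculated loss of first doses would measure a step that is not in the plan.
- *That comparisons between etiologies are distorted through the product used.* The documents give no separate schedule for combined products and no link between product and etiology.

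**Conclusion.** The point holds in a limited form. Two sections state an outcome rule that omits the minimum interval found in the protocol's own description of the series. Followed literally, the rule counts early second records as completed courses in both models. For that fault the direction is upward for two-dose coverage and towards shorter times to the second dose.

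The size cannot be derived from the documents. The 0.3 to 1.3 points rest on assumed early-record shares of 2% to 10% and on US coverage figures taken at one-third and one-fifth; they show scale and are not an estimate. A larger inflation, obtained by taking some share of all second records as false completions, would assume that nobody with an early record later receives a qualifying dose. It would be an upper bound on an assumed share.

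This is a definition to settle before extraction, not a flaw in the design. No view is taken on which interval is clinically right.

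**What to change.** 1. Reconcile the schedule in the Introduction and Variables sections with the outcome rule in Variables and Sensitivity Analysis. State whether a minimum interval applies to dose 2, and put whatever minimum the protocol adopts into both the 12-month and the 3-year definitions.
2. Report second records before that interval in a separate row, not as completion. Keep those people in the first-dose state and at risk for a later qualifying dose.
3. As a minor wording point, replace the remark in Sensitivity Analysis about recently vaccinated people. Say that recent first-dose recipients are kept and right censored at the end of data (31 December 2022), consistent with the multistate section.

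The cost is one clause in the outcome definition, one reworded sentence and one extra table row. No new data are needed and the model structure does not change.
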